## Abstract

**Background:**

Complaints of imbalance are common non-resolving signs in individuals with post-concussive syndrome. Yet, there is no consensus rehabilitation for non-resolving balance complaints following mild traumatic brain injury (mTBI). The heterogeneity of balance deficits and varied rates of recovery suggest varied etiologies and a need for interventions that address the underlying causes of poor balance function. Our central hypothesis is that most chronic balance deficits after mTBI result from impairments in central sensorimotor integration that may be helped by rehabilitation. Two studies are described to 1) characterize balance deficits in people with mTBI who have chronic, non-resolving balance deficits compared to healthy control subjects, and 2) determine the efficacy of an augmented vestibular rehabilitation program using auditory biofeedback to improve central sensorimotor integration, static and dynamic balance, and functional activity in patients with chronic mTBI.

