### Participants

The study will include 65 mTBI participants and 65 control subjects for the cross-sectional arm of the study. All subjects will be between the ages of 18 and 60. Participants in the mTBI group will have a diagnosed mTBI or concussion and chronic, non-resolving complaints of balance problems determined by a score >0 on the Dizziness Handicap Inventory (DHI) at the time of testing and > 3 months post-injury. Control subjects will be gender and age matched to the mTBI group. For the second arm of the study, a subset of 40 mTBI subjects with abnormal central sensorimotor integration with or without peripheral vestibular or ocular motor deficits will be randomized into two rehabilitation groups, experimental treatment and standard of care, consisting of two rehabilitation sessions per week for 6 weeks. All subjects will be tested at either Oregon Health & Science University or the VA Portland Health Care System. All rehabilitation will take place at Oregon Health & Science University. Informed written consent will be obtained from all participants.

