#### Statistical analysis

To determine if objective/novel measures of balance will better distinguish people with mTBI from control subjects than clinical measures, we will use logistic regression classification models. Improvements in classification will be determined by calculating the area under the curve (AUC) of the receiver-operator characteristic and then comparing AUC for each traditional clinical measure with the novel objective measures. Significance will be assessed using bootstrapping to determine if the observed differences in AUC are greater than would be expected by chance at a level of 0.05.

To determine if a subset of people with mTBI will have abnormal CSMI test measures, even without peripheral vestibular or ocular motor deficits, we will use descriptive statistics to characterize the distribution of CSMI test measures and vestibular/ocular motor scores. We will define CSMI test measures and vestibular/ocular motor scores as abnormal if the scores are greater than 2 standard deviations from the mean in controls. We will then classify mTBI subjects into one of 4 CSMI-vestibular/ocular motor categories 1) abnormal CSMI –abnormal vestibular/ocular motor scores, 2) abnormal CSMI –normal vestibular/ocular motor scores, 3) normal CSMI –abnormal vestibular/ocular motor scores, 4) normal CSMI –normal vestibular/ocular motor scores.

To determine if the observed relationship between poorer static/dynamic balance performance and mTBI is regulated/mediated by central sensorimotor integration, we will use mediation analysis. Mediation analysis [49] will allow for the partitioning of the association between mTBI and chronic imbalance into two parts, the direct relationship of mTBI on balance impairment as well as the causally mediated effect of mTBI on central sensorimotor integration, which, in turn is having the actual effect on imbalance. These varying generative mechanisms of balance deficits will be assessed by utilizing linear models relating mTBI to CSMI test measures alongside models of mTBI and CSMI test measures jointly affecting imbalance using the apportionment methods described by Baron and Kenny [49].

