If a portion of subjects with chronic balance problems after mTBI have abnormal CSMI test measures but normal clinical vestibular testing results, this suggests that sensory integration processes in the brain can be impaired following mTBI, even without peripheral sensory deficits, and that abnormal central sensorimotor integration plays a key role in persistent abnormal balance in subjects with normal vestibular function. If a portion of mTBI subjects have abnormal CSMI test measures and abnormal clinical vestibular function, the key mediator for balance problems is less clear and may be due to the peripheral vestibular dysfunction, abnormal central sensorimotor integration, or inadequate adaptation of central sensorimotor integration to account for abnormal sensory information. If we find that abnormal central sensorimotor integration mediates abnormal static or dynamic balance, rehabilitation will need to be focused on improving central sensorimotor integration to improve balance. If we find that CSMI scores improve with rehabilitation, we will conclude that central sensorimotor integration strategies are flexible and can improve with training. Further, if we find that central sensorimotor integration and gait and balance jointly improve with rehabilitation, we will have further evidence that central sensorimotor integration plays a key role in the mediation of gait and balance following mTBI. If we find a greater improvement in the ABF group, we will conclude that ABF may facilitate improved rehabilitation. Finally, if we find that people with central sensorimotor integration impairment maintain improvements after stopping the use of ABF device, we will conclude that a recalibration of sensory integration and/or sensorimotor transformation for balance has occurred, rather than sensory substitution that requires active ABF. If we find that sensory strategies can change with practice and biofeedback, we will conclude that this targeted approach to balance rehabilitation should be explored further in a larger, randomized trial. It is possible that different subclasses based on CSMI measures respond differently to rehabilitation or ABF-augmented rehabilitation. In such a case, the results of this study will provide valuable information for powering an in-depth future study carefully examining the relationship between CSMI subclasses and the response to rehabilitation with and without ABF. The results of this study will further our understanding of the mechanisms underlying posture and gait dysfunction in individuals with chronic mTBI and inform future studies about the efficacy of ABF augmented rehabilitation programs.

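### The Discussion infers that abnormal central sensorimotor integration drives imbalance in people with normal vestibular tests, but the classification behind that inference has no balance outcome and no control benchmark

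*Protocol article*

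**What the plan says.** In Study 1, Statistical analysis, the hypothesis that a subset of mTBI participants has abnormal CSMI is addressed descriptively: "we will use descriptive statistics to characterize the distribution of CSMI test measures and vestibular/ocular motor scores". A score is "abnormal if the scores are greater than 2 standard deviations from the mean in controls". Then: "We will then classify mTBI subjects into one of 4 CSMI-vestibular/ocular motor categories", that is, abnormal or normal CSMI crossed with abnormal or normal vestibular/ocular motor scores. Category 2 is abnormal CSMI with normal vestibular/ocular motor scores; category 4 is normal on both. No balance measure enters this step.

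The Discussion says how the result will be read: "If a portion of subjects with chronic balance problems after mTBI have abnormal CSMI test measures but normal clinical vestibular testing results, this suggests" two things. One is that integration can be impaired without peripheral deficits. The other is "that abnormal central sensorimotor integration plays a key role in persistent abnormal balance in subjects with normal vestibular function".

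The Study 1 analysis that links CSMI to balance is the mediation analysis, which uses "linear models relating mTBI to CSMI test measures alongside models of mTBI and CSMI test measures jointly affecting imbalance". The Discussion reads its result in a separate, later sentence.

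**The concern.** The two halves of the Discussion sentence need different evidence. That CSMI can be abnormal when vestibular tests are normal is a statement about prevalence, and a count can support it if the count exceeds what controls show. That abnormal CSMI plays a key role in poor balance is a statement about association, and ultimately cause. It needs balance to differ with CSMI among people whose vestibular tests are normal.

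The classification cannot show this. Under Participants and the inclusion criteria, every mTBI participant has a DHI score above 0, so a balance complaint is present in categories 2 and 4 alike. If category 4 balanced just as badly as category 2, the stated reading would not change.

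The condition is also easy to meet. The text asks only for a portion, with no minimum and no comparison with controls. At stake is a published mechanistic statement about the normal-vestibular group that the planned work for that group could not contradict.

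**Working it through.** The plan gives no figure for this reading rule, so there is none to reproduce. The check is in three parts.

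**1. How often the cut-off alone fills category 2**

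Inputs from the article: 65 mTBI participants (Participants) and a 2-SD cut-off (Study 1, Statistical analysis).

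Assumptions:
- mTBI participants follow the control distribution, which is normal with known mean and SD.
- The cut-off is two-sided.
- One CSMI measure counts.
- A share s has normal vestibular/ocular motor tests, independently of CSMI. The article does not give s.

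Flag rate per measure: 2 × (1 − Φ(2)) = 0.0455.

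Expected number in category 2: 65 × 0.0455 × s. Chance of at least one: 1 − (1 − 0.0455 s)^65.

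| s | Expected in category 2 | Chance of at least one |
|---|---|---|
| 0.3 | 0.9 | 59% |
| 0.5 | 1.5 | 78% |
| 0.7 | 2.1 | 88% |

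**2. More than one measure**

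Under Primary outcome measure, the model is fitted to each of 8 tests. Each fit yields one free sensory weight (or sum of weights) plus Kp, Kd, Kt and td, so 5 values per test and 5 × 8 = 40 in all. The article does not say how many must be abnormal for a person to count as abnormal. If any one is enough (assumed), the rate per person is 1 − (1 − 0.0455)^m when measures are independent; the correlated figures are simulated.

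| Measures counted | Independent | Correlation 0.5 | Correlation 0.8 |
|---|---|---|---|
| 5 | 20.8% | 16.9% | 11.7% |
| 40 | 84.5% | 53.9% | 26.1% |

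A sizeable share could therefore arise with no CSMI difference at all. The plan expects 40 participants with abnormal CSMI for Study 2, or 40/65 = 62%. Even a share of that size cannot be interpreted without the share of controls flagged by the same rule.

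**3. Does another planned analysis supply the missing comparison?**

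- *Mediation models, Study 1.* The exposure is mTBI status. As described, the models are neither restricted to nor stratified by normal vestibular function. They estimate a CSMI–balance association overall, not in the group that the sentence is about.
- *Study 2.* All 40 participants have abnormal CSMI, so there is no normal-CSMI comparison group. Its stratification by vestibular/ocular motor status concerns sustained improvement, not balance at entry.

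**Precision of the comparison, if added**

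Assume half of 65 (about 32) have normal vestibular tests and 40/65 of these have abnormal CSMI: 32 × 40/65 ≈ 20, leaving 12. A two-sample t-test at two-sided 0.05 with 80% power then detects a standardised difference of d = 1.06.

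The normal approximation d = (1.96 + 0.84) × √(1/n1 + 1/n2) gives 1.02 for the same split. For other assumed sizes, with half to a quarter having abnormal CSMI, it gives 1.19 to 1.34 with 22 people and 0.80 to 0.93 with 49.

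Parts 1 and 2 suppose no CSMI difference; this last part supposes the share that the plan expects. They are separate scenarios.

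**The case against.** The strongest reply is that the sentence is hedged and is not a decision rule. It says the finding suggests a key role, whereas other sentences in the same paragraph say what the investigators will conclude. No enrolment or treatment decision depends on it. That is true and limits the weight of the point, but the hedge does not supply the missing comparison.

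A second reply is that the CSMI–balance link is tested by mediation, that vestibular tests are collected as covariates, and that model terms may be left to the full protocol. This stands in part: vestibular terms may well be added. But the Discussion rests the key-role sentence on category membership, not on the mediation result.

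A third reply is that the magnitudes depend on inputs outside the article. They do: the normal-vestibular share, the number of measures counted and the 20/12 split are assumptions, and treating any non-zero count as a portion is the most lenient reading. A control benchmark is needed under any of these values.

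A reader might be tempted further in three ways, none of which the article supports:

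- *That Study 1 cannot fail on its central claim.* The hypothesis that CSMI mediates poor balance has its own models, and these can come out null.
- *That a portion falls short of the abstract's hypothesis that* "most chronic balance deficits after mTBI result from impairments in central sensorimotor integration". The classification serves a different hypothesis, about a subset. Category 1 (abnormal on both) also has abnormal CSMI, so the category 2 share is the wrong quantity to set against that claim. The Background's restatement of the central hypothesis also omits the word most.
- *That category 2 against category 4 is the only valid contrast.* A regression on continuous CSMI values within the same group answers the question too, and avoids dichotomising.

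**Conclusion.** The concern holds in a limited form. The key-role reading for people with normal vestibular function rests on a classification with no balance outcome, no control benchmark and no minimum share. The cut-off alone gives a 78% chance of a non-empty category 2 under one measure and a 50% normal-vestibular share (59% to 88% for shares of 30% to 70%), and more if several measures count. These figures assume no mTBI–control difference and a normal control distribution.

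Prevalence can support the first half of the sentence if it exceeds the control rate. It cannot support the second half. The whole-sample mediation analysis is a genuine test of the CSMI–balance link, but as described it is not specific to this group. The point should be corrected before analysis. It affects the interpretation of one Study 1 result and does not invalidate the study.

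**What to change.** 1. Among mTBI participants with normal vestibular/ocular motor tests, regress the static and dynamic balance measures on CSMI (continuous, or category 2 versus category 4), adjusted for age and gender. Report the estimate with a 95% CI.
2. Report the share with abnormal CSMI beside the share of controls flagged by the same rule.
3. Make the key-role statement only if the estimate in step 1, read with the mediation result, supports it. Otherwise limit the sentence to co-occurrence: CSMI can be abnormal when vestibular tests are normal, provided step 2 shows an excess over controls.

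Cost: one added regression on data already collected, one added control percentage and a reworded sentence. The downside is a wide interval, with only about d = 1.06 detectable at 80% power under the assumed 20/12 split. A null result should therefore be read as imprecise, not as evidence of no association. The comparison is cross-sectional, so even a clear association would not by itself establish cause.

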### Study 2: Rehabilitation of balance deficit

#### Assessment procedures

Subjects with mTBI who participate in Study 1 will be screened for Study 2. An investigator will verbally explain the consent form and time commitments involved with the rehabilitation, allow the person ample time to read through the consent form and then will acknowledge consent by signing the form. For Study 2, 40 mTBI participants will participate in a 6-week rehabilitation program randomized to either 1) a standard vestibular focused rehabilitation program or 2) the same standard vestibular focused rehabilitation program with the addition of audio biofeedback. Post-rehabilitation assessments will be conducted one week after the conclusion of the program. Retention will be assessed 6 weeks following the post-rehabilitation session. A flowchart illustrating the study design is depicted in Fig. 3.

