#### Intervention

Participants will be randomized into either 1) a standard of care vestibular rehabilitation program or 2) a standard or care vestibular rehabilitation plus ABF training program. Rehabilitation will begin approximately 7-10 days after pretest assessment. Both groups will receive the rehabilitation that includes progressive (3 levels of difficulty) exercises that target gaze stabilization, vestibular stimulation, balance and proprioceptive retraining [50–52] (Table 5). Subjects randomized to the ABF training, will undergo the same vestibular rehabilitation program but will wear an ABF device while performing the rehabilitation exercises. All researchers performing post-rehabilitation testing will remain blinded to the randomized group assignment throughout the duration of the study.

**Table 5 Tab5:** Rehabilitation protocol

Exercise	Vision	Surface	Time	Progression	ABF
Static Balance	Eyes open	Firm	30 s per condition	10 double stance conditions including tossing a ball, head rotations left-right, head rotations up-down, head rotations with smooth pursuit, with gaze stabilization, and with saccades	Pitch modulated feedback for AP sway, direction modulated for ML sway
	Eyes closed	Firm	30 s per condition	3 double stance conditions including head rotations left-right, head rotations up-down	
	Eyes open	Foam	30 s per condition	4 double stance conditions including tossing a ball, head rotations left-right, head rotations up-down	
	Eyes closed	Foam	30 s per condition	3 double stance conditions including head rotations left-right, head rotations up-down	
Dynamic Balance (Tandem Gait)	Eyes open	Firm	30 s per condition	4 tandem gait conditions including tossing a ball, head rotations left-right, head rotations up-down	Direction modulated for ML sway
	Eyes closed	Firm	30 s per condition	1 tandem gait condition	
	Eyes open	Foam	30 s per condition	4 tandem gait conditions including tossing a ball, head rotations left-right, head rotations up-down	
	Eyes closed	Foam	30 s per condition	1 tandem gait condition	
Dynamic Balance (Bending down)	Eyes open	Firm	30 s per condition	3 different heights	Direction modulated for ML sway
	Eyes closed	Firm	30 s per condition	3 different heights	
Dynamic Balance (Squatting)	Eyes open	Firm	30 s per condition	4 squats including sit-to-stand, lunge, lunge onto unstable surface, and lunge + twist	Direction modulated for ML sway

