#### Statistical analysis

To determine if ABF intervention improves central sensorimotor integration, we will build linear regression models to simultaneously evaluate the change in CSMI measures reflecting central sensorimotor integration and the effect of ABF compared to standard of care. Our outcome will be the change in pre- versus post-rehabilitation program CSMI measures; using the change (difference) in CSMI measures will control for the correlation of the repeated pre- and post- measures within an individual as well as maximizing the number of covariates we can potentially add into the regression models. Covariates of interest are vestibular/ocular motor scores, PTSD, Veteran versus civilian status, age, and gender. In addition, we will determine whether rehabilitation improved the static and dynamic balance metrics that were measured at the pre- and post-rehabilitation testing visits.

To determine if people with CSMI impairment show sustained improvement in static and dynamic balance after rehabilitation, even after ABF is discontinued, we will use linear mixed effects regression modeling which will include a third time point of interest (6 weeks after the rehabilitation intervention has stopped). Time will be treated as a categorical variable in order to evaluate changes in CSMI scores and balance during specific time periods, in this case, between the cessation of the intervention and the 6 weeks post-intervention follow-up. We will explicitly test the significance of a group by time interaction to determine if participants in the ABF rehabilitation group showed sustained improvements in outcomes beyond that experienced by participants with the standard of care. If applicable, we will then stratify the analysis by those with abnormal/normal measures of vestibular/ocular motor function to assess the relationship between vestibular/ocular motor function deficits and sustained improvement in CSMI score and balance.

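### Study 2 would read joint improvement in CSMI and balance as further evidence of mediation, but its stated design and analyses cannot tell mediation from two parallel training effects

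*Protocol article*

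**What the plan says.** **The inference.** The Discussion states the condition: "if we find that central sensorimotor integration and gait and balance jointly improve with rehabilitation, we will have further evidence". What this is said to support is a key mediating role of CSMI in gait and balance. Joint improvement is the only condition named.

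**The training.** Under Study 2, Assessment procedures, one arm receives the standard vestibular programme and the other receives "the same standard vestibular focused rehabilitation program with the addition of audio biofeedback". The Intervention section describes the shared content as "exercises that target gaze stabilization, vestibular stimulation, balance and proprioceptive retraining". Table 5 lists stance with eyes open and closed on firm and foam surfaces, tandem gait, bending and squatting.

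**The analysis.** Under Study 2, Statistical analysis, the first model concerns CSMI: "Our outcome will be the change in pre- versus post-rehabilitation program CSMI measures", with a comparison of arms. The covariates are then listed: "Covariates of interest are vestibular/ocular motor scores, PTSD, Veteran versus civilian status, age, and gender". Balance is a separate question: "In addition, we will determine whether rehabilitation improved the static and dynamic balance metrics". Retention is analysed by mixed models with a group-by-time interaction. The only stratification is by vestibular and ocular motor function.

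**Mediation elsewhere.** Study 1, Statistical analysis, sets out a mediation analysis with injury status as exposure, CSMI as mediator and balance as outcome. It uses measurements from a single occasion.

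**The concern.** If the programme improves balance by one route and CSMI by another, both will improve and the Discussion will count this in favour of mediation. The four surface and vision combinations practised in stance are also those of the Clinical Test of Sensory Organization and Balance (CTSIB), listed as an outcome in Table 3. Task practice is therefore a plausible direct route for static balance.

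Two further features make joint improvement easy to obtain. Without an untreated arm, improvement with rehabilitation is an uncontrolled before-after change. And participants enter Study 2 because their CSMI is abnormal, defined in Study 1 as more than 2 standard deviations from the control mean. Methods / Design describes one baseline test, a repeat after rehabilitation and a third at retention. The qualifying measurement thus appears to serve also as the pre-test, and part of any CSMI improvement could be regression to the mean.

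Study 2 supplies the only longitudinal evidence on the central hypothesis that chronic imbalance results from impaired integration. The Discussion also says that a finding of mediation would direct where rehabilitation should focus. An unsupported mechanistic statement here could shape the larger trial that Study 2 is meant to inform.

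**Working it through.** The plan states no figure on this point, so there is none to reproduce. Three checks were made.

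**1. Does any stated Study 2 analysis link the two changes?**
- CSMI change model: terms for arm and the listed covariates. Balance change is not among them.
- Balance question: before versus after. No CSMI term is stated.
- Retention model: group, time and their interaction, with no model of one outcome on the other.
- Study 1 mediation analysis: links CSMI and balance across persons at one time, not as changes.

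No stated Study 2 analysis does so.

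**2. How often would both improve with no within-person link?**

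Inputs: n = 40 (Participants section). Assumptions: CSMI change and balance change independent within persons, each with mean standardised change d; each tested by a one-sample t-test at two-sided 0.05; their association tested by a Pearson correlation; 20,000 simulated cohorts per value of d. The value 0.748 is borrowed from the Study 2 sample-size section only as one point in the range. The plan does not give it as an expected before-after change in both outcomes.

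| Assumed d | Both improve significantly | Correlation of changes significant |
|---|---|---|
| 0.3 | 21% | 4.9% |
| 0.5 | 76% | 4.6% |
| 0.748 | 99% | 5.1% |
| 1.0 | 100% | 4.7% |

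The same follows by multiplication. If each mean change is detected with probability p and the two are independent, both are detected with probability p²: 0.80 × 0.80 = 0.64 and 0.90 × 0.90 = 0.81. The percentages depend on the assumed effects. What does not depend on them is that joint improvement becomes near certain as the two training effects grow, whether or not they are linked, while the correlation test stays at its nominal level.

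**3. Is a within-person analysis feasible at this size?**

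For a partial correlation r with k adjustment terms, the Fisher statistic is approximately atanh(r) × √(n − 3 − k). Adjusting for arm, baseline CSMI and baseline balance gives k = 3, and √(40 − 3 − 3) = √34 = 5.83.
- r = 0.45: 0.485 × 5.83 = 2.83; 2.83 − 1.96 = 0.87; power about 80%.
- r = 0.43: 0.460 × 5.83 = 2.68; 2.68 − 1.96 = 0.72; power about 76%.

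Without adjustment, r = 0.43 gives 0.460 × √37 = 2.80; 2.80 − 1.96 = 0.84; power about 80%. All of these assume 40 complete pairs, so dropout would lower them.

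**The case against.** The strongest defence is that this is a remark in the Discussion, not a decision rule. Nearby sentences say what the authors will conclude; this one speaks only of further evidence. The word further points back to Study 1, where mediation is formally analysed. None of the Study 2 hypotheses is a mediation hypothesis, and Methods / Design calls Study 2 a pilot. Joint improvement is what mediation predicts, and its absence would count against mediation, so observing it is weak but real support. All of this stands. It limits the point to an over-strong inference.

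Four stronger readings that a reader might infer are not supported:
- *That the plan commits to declaring mediation whenever two group means improve.* The text sets no such test. The percentages above illustrate poor discrimination and are not an error rate of the trial.
- *That the gait outcomes are practised directly.* Table 5 trains tandem gait, whereas the gait tests in Table 3 are comfortable, dual-task and turning walking. The overlap lies in static balance, and even there practice is in 30 s progressions and the CTSIB in 60 s of stance.
- *That CSMI must move for unrelated reasons.* The Background says that standing or walking on foam demands sensory reweighting, so the same exercises may train both. That makes mediation plausible, but it equally describes one training programme with two effects.
- *That a change-on-change slope would settle the matter.* Effort, adherence or test familiarity could move both outcomes in the same people.

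It may also be said that a change-on-change model could sit in a full protocol or analysis plan not shown. Its absence from a condensed article would not by itself be a finding. The article does, however, state an inference whose only condition is joint improvement, and an unseen model would not correct that sentence.

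**Conclusion.** The point holds in limited form. Joint improvement after rehabilitation is compatible with mediation by CSMI. In this design it is also compatible with parallel training effects and, on the CSMI side, with regression to the mean. Calling it further evidence of a key mediating role claims more than the stated Study 2 analyses can deliver.

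No primary estimate, test or sample size changes; what changes is a mechanistic conclusion. The size of the problem can only be illustrated: with no within-person link, both outcomes improve significantly in 21% to essentially all cohorts of 40 for assumed standardised changes of 0.3 to 1.0. The concern about regression to the mean rests on the qualifying CSMI test also being the pre-test, which the text implies but does not state outright.

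**What to change.** 1. In the Discussion, say that joint improvement alone is *consistent with* a mediating role for CSMI, and that balance training in both arms and the lack of an untreated arm leave other explanations open.

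2. In Study 2, Statistical analysis, add a prespecified exploratory regression of change in balance on change in CSMI, adjusted for arm and the baseline values of both measures. Fit it once for a named static measure and once for a named dynamic measure. Name the single CSMI parameter and its test condition in advance: Table 2 lists seven parameters, the fit is repeated for each of eight tests, and the Study 2 primary outcome singles out none.

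3. Cite Study 2 as supporting mediation only if the slope is in the predicted direction and its interval excludes zero. State that such a slope supports mediation but does not prove it. Otherwise report joint improvement as a response to training.

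The cost is two regression models on data already collected and a few sentences. A mediation statement becomes harder to make. The models will also be imprecise: with 40 complete pairs, only a partial correlation of about 0.45 or more is detectable with roughly 80% power, so a null slope should not be read as evidence against mediation.
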